# Acupuncture (Jin’s Three-Needle) versus sham acupuncture in treating mild-to-moderate depression: Study protocol for randomized clinical trial

**DOI:** 10.1371/journal.pone.0338341

**Published:** 2025-12-05

## Abstract

**Background:**

Mild-to-moderate depression is an increasing public health problem worldwide, which is more prevalent than major depression but has received less attention Currently, no existing highly effective pharmacological treatments with minimal adverse reactions are available for this condition. Jin’s Three-Needle Acupuncture (JTN) may be an alternative treatment option for mild-to-moderate depression patients.

**Methods:**

This is a prospective, parallel-arm, single-blind, randomized controlled trial. We plan to enroll 106 participants with mild-to-moderate depression, randomly assigning them to receive either JTN or sham acupuncture (SA) in a 1:1 ratio. All participants will receive the JTN treatment or SA treatment for 8 weeks (3 per week). The primary outcome will be assessed using the 17-item Hamilton Depression Rating Scale (HAMD-17). Secondary outcomes will include the Self-Rating Depression Scale (SDS), Pittsburgh Sleep Quality Index (PSQI), Hamilton Anxiety Scale (HAMA), Self-Rating Anxiety Scale (SAS), and the Traditional Chinese Medicine Syndrome Score Scale (TCMSS). Evaluations will be performed at baseline and at weeks 4, 6, and 8 after treatment initiation. Statistical analyses will be conducted on both the intention-to-treat (ITT) and per-protocol (PP) datasets.

**Discussion:**

This study aims to provide high-quality evidence regarding the efficacy and safety of JTN as a treatment for mild-to-moderate depression. Additionally, the mechanisms underlying the effects of JTN in treating mild-to-moderate depression will be explored.

**Trial registration:**

The trial registered with the International Traditional Medicine Clinical Trial Registry (ITMCTR2024000872). URL: https://www.itmctr.ccebtcm.org.cn

## Introduction

Depression, a prevalent psychiatric disorder characterized by persistent low mood, represents a significant contributor to the global disease burden and a leading cause of disability [1]. In China, previous studies [2] have shown that the annual prevalence rate of depression in China was merely 2.06% between 2001 and 2005, but this figure rose to 10.6% by 2022 [3]. A particular difficulty in treating depression lies in the large number of people experiencing mild to moderate symptoms. Despite making up a substantial portion of those affected, these individuals often fall through the cracks of clinical care. Without proper intervention at this stage, their condition may worsen into more severe forms of depression [4]. Consequently, investigating potential improvements in the treatment of mild-to-moderate depression is of critical importance.

Current treatment guidelines present clinicians with something of a dilemma. First-line antidepressant pharmacotherapy, while effective for many, is often associated with a range of adverse effects that can impact cardiovascular, gastrointestinal, and endocrine systems, raising concerns about their suitability for milder clinical presentations [5–7]. International guidelines indeed advise caution in the routine prescription of antidepressants for mild-to-moderate cases, often recommending initial monitoring or psychotherapy [8,9]. However, psychological therapies such as cognitive behavioural therapy (CBT) are highly dependent on the availability of trained psychotherapists, making them difficult to implement in low-income areas [10]. Therefore, it is crucial to seek a potential treatment that is safe, accessible, affordable, and effective.

Jin’s Three-Needle (JTN), a distinct form of acupuncture, has been clinically applied for decades and is recognized as a unique school of acupuncture in Southern China. JTN demonstrates therapeutic efficacy in treating mental disorders and assisting patients in modulating their mental states [11]. Our earlier research shows that JTN treatment may considerably reduce the major symptoms of depression for opioid dependence patients [12]. Recent studies have demonstrated that peripheral blood leukocytes from patients with depression exhibit elevated expression levels of depression-related genes, particularly inflammatory markers, which often display DNA methylation patterns resembling those observed in brain tissues [13,14]. For instance, methylation of the glucocorticoid receptor gene NR3C1 and the serotonin transporter gene SLC6A4 in leukocytes has been linked to depressive symptoms [15,16]. DNA methylation in peripheral blood leukocytes represents a promising biomarker for depression, as it frequently suppresses or blocks the transcription of genes associated with depressive symptoms [17,18]. Research has indicated that acupuncture can reduce the production of pro-inflammatory cytokines [19]. Previous studies found that acupuncture treatment significantly decreased the serum levels of IL – 6 and TNF – α in patients with major depressive disorder. Acupuncture may suppress the activation of the nuclear factor – kappa B (NF-κB) signaling pathway in the brain of rats with depression – like behavior. The NF-κB pathway is a key regulator of inflammatory responses, and its inhibition by acupuncture may lead to a reduction in the production of inflammatory cytokines, thus exerting an anti-depressive effect [20]. We hypothesize that JTN treatment may modulate aberrant gene expression and DNA methylation patterns in the peripheral blood leukocytes of individuals with depression, potentially resulting in improved depressive symptoms. Therefore, the present study aims to (1) assess the efficacy and safety of JTN treatment for mild-to-moderate depression and (2) investigate the potential mechanisms underlying JTN’s therapeutic effects in treating depression.

## Methods

### Trial design

This study is designed as a prospective, single-center, single-blind, randomized, controlled trial to evaluate the efficacy and safety of acupuncture (Jin’s Three-Needle) for Mild-to-Moderate Depression. This study protocol conforms to the Consolidated Standards of Reporting Trials (CONSORT 2025) guidelines [21], the Standard Protocol Items: Recommendations for Interventional Trials (SPIRIT2025)(See S1 in the Supplementary file in S1 File) [22], and the Standards for Reporting Interventions in Controlled Trials of Acupuncture (STRICTA) (See S2 in the Supplementary file in S1 File) [23]. The flowchart of the trial design is depicted in Fig 1.

**Fig 1 pone.0338341.g001:**
[figure not shown]
Flowchart of trial procedures. Notes: HAMD-17: The 17-item Hamilton Depression Rating Scale; SDS: Self-rating depression scale; PSQI, Pittsburgh sleep quality index; TCMSS: The traditional Chinese medicine syndrome score scale; HAMA: Hamilton Anxiety Scale; SAS: Self-Rating Anxiety Scale.

The trial will be conducted in accordance with the Declaration of Helsinki and has been approved by the Ethics Committee of Guangzhou Huangpu District Hospital of Traditional Chinese Medicine (TCMHHP2024120401) and registered with the International Traditional Medicine Clinical Trial Registry (ITMCTR2024000872). This trial is currently recruiting patients, which started on 01 January 2025 and is anticipated to end on 12 December 2026.

### Setting

The trial will be conducted in the outpatient department of Guangzhou Huangpu District Hospital of Traditional Chinese Medicine

### Participants

Participants will be recruited through advertisements at Guangzhou Huangpu District Hospital of Traditional Chinese Medicine. Only those participants who meet all inclusion criteria will be recruited for the study after they sign the informed consent form.

### Inclusion criteria

Participants who meet the following criteria will be included.

① Patients who fit the diagnostic criteria for depression in the Diagnostic and Statistical Manual of Mental Disorders(DSM-5);② Patients with a HAMD-17score between 8 and 25.③ Patients between the ages of 18 and 65 years;④ Patients are voluntary and able to sign informed consent.

### Exclusion criteria

① Patients having suicidal tendencies (HAMD third score greater than 2 points), bipolar depression, and treatment-resistant depressions;② Patients having immediate family or personal history of mental illness;③ Patients who have serious physical health (as assessed by a doctor);④ Patients who are pregnant or planning to become pregnant;⑤Patients who have taken antidepressants or receive acupuncture treatment within three months.⑥Patients with contraindications to acupuncture, including: a. Coagulation disorders (e.g., hemophilia) or current use of anticoagulant medication (e.g., warfarin); b. Severe thrombocytopenia; c. Local skin infections, ulcers, or scars at proposed needling sites; d. Presence of an implanted electronic medical device (e.g., pacemaker, spinal cord stimulator); e. Known severe cardiovascular conditions (e.g., uncontrolled arrhythmia).

### Randomization and allocation concealment

Researchers who are unaware of the trial will use SAS statistical software (SAS Inc., NCSU, version: 9.4, USA) to generate random numbers. The randomization sequence will be created using permuted blocks with a 1:1 allocation ratio (block size = 4) through a computer-generated process. The block size shall not be revealed until the end of the trial. Participants will be informed that they have an equal chance to be assigned to the acupuncture (Jin’s Three-Needle) group or sham acupuncture group.

All the randomization number will be placed in opaque, sealed envelopes. After eligible participants sign the informed consent form and complete baseline assessments, they will receive a sealed envelope with the assigned number. Allocation concealment will be strictly implemented through an independent procedure conducted by an independent researcher at the clinical site, maintaining strict separation between randomization and outcome evaluation processes.

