### Blinding

Acupuncturists will not be blinded to group allocation. However, the two groups of participants will avoid getting communicating with each other after randomization, and will receive treatment in separate treatment rooms to minimize subjective effects. The outcome assessors, data collectors, and statisticians will be blinded to group allocations. An independent researcher will supervise the conversation between participants and acupuncturists to avoid them communicating issues related to the allocation. At mid-study and end-study, participants will be asked via anonymous questionnaires to guess their assigned group and provide reasons. Statistical analysis of the results will be used to check whether participants remained blinded. If a significant number guess correctly, potential causes will be analyzed and measures will be adjusted. After each assessment, assessors will reassess the group allocations of randomly selected cases without access to their prior assessment results, while their decision-making processes will be recorded. The comparison between initial and repeated judgments will be used to assess whether assessors will be influenced.

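### The article promises to withhold the block size until the trial ends but prints it as a fixed 4 during recruitment, so someone with the running order could know about one third of later allocations

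*Protocol article*

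**What the plan says.** The section on randomization and allocation concealment specifies "permuted blocks with a 1:1 allocation ratio (block size = 4) through a computer-generated process". No second or varying size is given and no stratification is described. The next sentence is "The block size shall not be revealed until the end of the trial".

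The other safeguards in that section are physical and procedural. "All the randomization number will be placed in opaque, sealed envelopes", each participant receives an envelope after consent and baseline assessment, and an independent researcher at the site carries out the allocation. The separation described there is between randomization and outcome evaluation.

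The setting comes from three other places:

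- The trial design section describes a "prospective, single-center, single-blind, randomized, controlled trial".
- The text below Figure 1 says "This trial is currently recruiting patients, which started on 01 January 2025 and is anticipated to end on 12 December 2026". The publication date at the head of the article is 2025-12-05.
- The blinding section says "Acupuncturists will not be blinded to group allocation" and that the two groups "will receive treatment in separate treatment rooms to minimize subjective effects". Outcome assessors, data collectors and statisticians are blinded.

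**The concern.** The two adjacent sentences cannot both hold in a published document. The plan treats secrecy of the block size as part of concealment, and the article removes that secrecy with about a year of the trial still to run.

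A sealed envelope hides its own contents. It does not stop a person from working out those contents when the block size is known and the earlier allocations in the block have been seen. A single centre without stratification has one running sequence, so there is only one count to keep. Unblinded acupuncturists and separate rooms make assignments visible on site.

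What is at stake is who enters the trial, and when. Some eligibility decisions leave room for judgement, such as the HAMD-17 range and the doctor's assessment of serious physical illness. If an upcoming allocation is known, entry can be brought forward, delayed or declined according to expected response. Selection on unmeasured prognosis of that kind cannot be reliably adjusted away, and the planned difference is small: 10.79 − 9.82 = 0.97 HAMD-17 points.

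**Working it through.** **Inputs from the article.** Block size 4, 1:1 allocation, N = 106, recruitment from 01 January 2025, publication on 2025-12-05, anticipated end 12 December 2026, SDs of change 1.40 and 1.80.

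**The plan's own figure.** Pooled SD = √((1.40² + 1.80²)/2) = 1.612. With a difference of 0.97, two-sided 5% and 80% power, the t-based calculation gives 45 per group (power 0.797 at 44 and 0.806 at 45). Then 45/0.85 = 52.9, rounded up to 53 per group, or 106. The sample size reproduces and this point does not affect it.

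**Predictability of a fixed block of 4.** The observer is assumed to know the block size and all earlier allocations in order. There are six equally likely balanced blocks.

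- Certain allocations: the fourth is always forced, and the third is forced in 2 of 6 blocks (those that open with two of the same arm). The mean is 1 + 2/6 = 1.33 of 4, or 33.3%.
- Best guess (the arm with more places left): the chance of being right at positions 1 to 4 is 1/2, 2/3, 2/3 and 1. The mean is 2.83/4 = 70.8%, against 50% with no information.

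**How many participants this covers.** Accrual is assumed even over the stated period.

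- From start to stated end is 710 days. From publication to stated end is 372 days.
- Still to be randomised at publication: 106 × 372/710 = 55.5, about 55. One third of 55 is about 18 certain allocations.
- If the end date is instead the last participant's final visit, enrolment closes 56 days earlier, on 17 October 2026. Then 106 × 316/654 = 51 remain, of which about 17 are certain.
- If site staff knew the block size from the first participant: 26 full blocks × 1.33 = 34.7, about 35 of 106.

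**Illustration of size, with an assumed input.** Suppose steering within the certain allocations makes expected change 1 point larger in the acupuncture arm than in the sham arm. The article gives no such figure.

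- Standard error with 45 per arm: √((1.40² + 1.80²)/45) = 0.340.
- 18 of 106 steered: bias = 18/106 × 1 = 0.17 points. Bias/SE = 0.50. With no true effect, the two-sided rejection rate is 1 − Φ(1.46) + Φ(−2.46), about 8% instead of 5%.
- One third of all allocations steered: bias 0.33, ratio 0.98, rejection rate roughly 16%.

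**What varying blocks would change.** Sizes 4/6 and 4/6/8 are assumed and were simulated.

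- Best-guess success falls only slightly, from about 71% to about 69% and 68%.
- Counting only allocations forced by the running imbalance, certainty is about 1% or less. That is a lower bound.
- An observer who knows the set of possible sizes and updates on the full history would be certain of about 6% (4/6) or 2% (4/6/8), against 33% for the fixed block. An observer who does not know the set has no firm basis for certainty.

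**The case against.** The strongest reply is that the route to bias is partly assumed. Steering needs someone, or people sharing information, who both know the ordered history and influence entry. The article says that acupuncturists are unblinded and refers to them in the plural. It does not say that any of them sees every patient, knows the order of randomisation, or screens, consents or enrols. Envelopes are given out only after eligibility and baseline are settled, an independent researcher runs the allocation, and outcome assessors are blinded. A fixed block of 4 is also not an error in itself.

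Most of this stands, and it limits the point in three ways. A reader might infer that acupuncturists know all past allocations and can foresee every coming one. The documents do not support that: about a third are certain, and only to someone with the running order. A reader might take 35 of 106 as the exposure caused by publication. That count includes people randomised before the article appeared and needs the site to have known the block size from the start, which is not stated. A reader might also conclude that selection has happened. Nothing in the article shows it, and bias would further require staff to foresee who will improve more.

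The reply does not restore the safeguard. The independent researcher and the envelopes limit who could act on a prediction but do not prevent one. No barrier is described between those who know past allocations and those who screen or enrol.

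**Conclusion.** The contradiction is certain on the text alone: the article discloses, during recruitment, a block size that it says will be withheld to the end. The consequence is conditional. For a person with the running order, one third of allocations after publication are certain and about 71% can be guessed. That is about 18 of roughly 55 remaining participants under even accrual to the stated end date, or about 17 of 51 if enrolment closes eight weeks earlier. The bias illustration rests on an assumed 1-point steering effect and shows only that modest steering would be noticeable beside a 0.97-point target. The finding is a vulnerability in concealment. It should be repaired promptly, because a repair protects only those not yet randomised.

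**What to change.** 1. For participants not yet randomised, have an independent statistician generate a new sequence with randomly varying block sizes. Keep both the sizes and the set they are drawn from away from site staff until the end of the trial. Replace the remaining envelopes and record the switch date.
2. State that those who screen and enrol are kept unaware of earlier allocations. This is the most direct control, because varying blocks remove most of the certain allocations but leave the best-guess rate at about 68–69%.
3. Correct the non-disclosure sentence to say that the original block size was disclosed, and when. Deleting the figure would not undo publication.
4. For participants randomised before the switch, compare baseline HAMD-17 according to the allocation predicted from block position, before and after publication. This can show selection on baseline severity. It cannot exclude selection on unmeasured prognosis.

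The cost is a short amendment, one new list and new envelopes, with no added patients or visits and no change to the sample size. The final arm sizes may differ slightly more. A block of 4 cut short leaves a difference of at most 2. A last block of up to 8 (assumed) leaves at most 4, plus up to 2 if the old list is stopped in mid-block.

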### Blinding

Acupuncturists will not be blinded to group allocation. However, the two groups of participants will avoid getting communicating with each other after randomization, and will receive treatment in separate treatment rooms to minimize subjective effects. The outcome assessors, data collectors, and statisticians will be blinded to group allocations. An independent researcher will supervise the conversation between participants and acupuncturists to avoid them communicating issues related to the allocation. At mid-study and end-study, participants will be asked via anonymous questionnaires to guess their assigned group and provide reasons. Statistical analysis of the results will be used to check whether participants remained blinded. If a significant number guess correctly, potential causes will be analyzed and measures will be adjusted. After each assessment, assessors will reassess the group allocations of randomly selected cases without access to their prior assessment results, while their decision-making processes will be recorded. The comparison between initial and repeated judgments will be used to assess whether assessors will be influenced.

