### Sample size calculation

The sample size was determined by utilizing the HAMD-17 scale score as the evaluative index. Based on previous study [33], after 8 weeks of treatment, the HAMD-17 score difference between the baseline and the endpoint in the acupuncture group should be approximately 10.79 ± 1.40, while the sham acupuncture group should be approximately 9.82 ± 1.80. Type 1 error is assumed at 0.05, and type 2 error is assumed at 0.2. PASS11.0 software (NCSS Statistical Software, Kaysville, UT, USA) has been used to determine the sample size, and the minimum sample size is 45 subjects for each group. Considering a dropout rate of 15%, a total of 106 subjects will be required with 1:1 allocation to each group (53 participants per group) for this study.

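### The assessor blinding check measures repeatability rather than unblinding, and the participant check names no link between a guess and the assigned arm

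*Protocol article*

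**What the plan says.** Both checks are in the Blinding section of the protocol article.

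**Participants.** At mid-study and end-study, "participants will be asked via anonymous questionnaires to guess their assigned group and provide reasons". The stated purpose is that "Statistical analysis of the results will be used to check whether participants remained blinded". The trigger for action is "If a significant number guess correctly, potential causes will be analyzed and measures will be adjusted". The section does not say how a form is tied to the arm of the person who filled it in, nor that forms carry no arm code. It does say that the two groups "will receive treatment in separate treatment rooms to minimize subjective effects".

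**Assessors.** After each assessment, "assessors will reassess the group allocations of randomly selected cases without access to their prior assessment results", and the reasoning behind their decisions is recorded. The inference rests on one sentence: "The comparison between initial and repeated judgments will be used to assess whether assessors will be influenced". True allocation does not enter that comparison.

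The same section states that acupuncturists know the allocation, while outcome assessors, data collectors and statisticians do not.

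**The concern.** A blinding check has to compare what people believe with what is true. The assessor check compares belief with belief, so it answers a different question from the one it is meant to answer. The participant check does need the truth, because its trigger is a count of correct guesses, but the text does not say where the truth comes from.

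This matters because the arms differ in ways a participant can feel. Under Intervention, true needling goes 5 to 30 mm deep, is rotated to produce de qi and is restimulated every 10 minutes. Sham needling stays under 5 mm with no manipulation. The primary outcome is the HAMD-17, scored by blinded assessors. The planned between-group difference is small: the Sample size section assumes that "the acupuncture group should be approximately 10.79 ± 1.40" against 9.82 for sham, a difference of 0.97 points. A modest expectancy or rating bias could matter at that scale, so readers will want blinding data that can be interpreted.

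**Working it through.** **Inputs.** The Sample size section gives mean changes of 10.79 (SD 1.40) and 9.82 (SD 1.80), alpha 0.05, type 2 error 0.2, 15% dropout, and 53 per group or 106 in total. The Statistical analysis section gives two-sided tests. Randomization uses "permuted blocks with a 1:1 allocation ratio (block size = 4"). Blinding states no figure of its own.

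**The plan's own figure (context only).** The difference is 10.79 − 9.82 = 0.97. The common SD is √((1.40² + 1.80²)/2) = √2.60 = 1.612. A two-sided t-test calculation gives power 0.797 at 44 per group and 0.806 at 45, so 45 reproduces. Then 45/0.85 = 52.9, rounded up to 53 per group and 106 in total. The number of people who could be asked to guess is therefore sound.

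**Assessor check.** Let p be the probability that a single allocation judgment is correct. If the repeat is independent of the first judgment given the true arm, expected agreement is p² + (1 − p)². If the assessor simply repeats the first judgment, agreement is 1 whatever p is.

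| True accuracy p | Agreement, independent repeat | Agreement, guess repeated |
|---|---|---|
| 0.50 (blinded) | 0.50 | 1.00 |
| 0.75 | 0.625 | 1.00 |
| 1.00 (fully unblinded) | 1.00 | 1.00 |

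A simulation of 400,000 judgments per cell gave the same values to within 0.002. Agreement of 100% therefore fits any accuracy from 50% to 100%. Low agreement would argue against full unblinding, but high agreement shows nothing either way.

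**Participant check with no link to arm.** Suppose all 106 respond, 53 per arm, and G of them guess true acupuncture. Let a be the number in the true arm who guess it. Then G − a in the sham arm guess it, and

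correct = a + (53 − (G − a)) = 2a + 53 − G, with a between max(0, G − 53) and min(53, G).

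- G = 53: a runs from 0 to 53, so correct runs from 0 to 106.
- G = 66: a runs from 13 to 53, so correct runs from 26 + 53 − 66 = 13 to 106 + 53 − 66 = 93, or 12% to 88%.
- G = 106: a = 53, so correct is exactly 53.

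The pooled total is nearly uninformative unless almost everyone gives the same answer.

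**Participant check with a link to arm.** With 106 coded forms, 64 or more correct (60.4%) differs from 50% at two-sided 0.05 by an exact binomial test. The chance of reaching that is about 51% if the true correct rate is 60% and about 86% if it is 65%; both rates are assumptions. Per arm, the 95% CI half-width around 50% is 1.96 × √(0.25/53) = 0.135 with all 53 responding, and 1.96 × √(0.25/45) = 0.146 with 45.

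**The case against.** The strongest reply concerns the participant half. A reader might infer that anonymous guesses can never be compared with allocation, that no arm-level index can be computed, or that the forms carry no information at all. The documents support none of these. Anonymous means that the person is not identified. A form can be anonymous and still bear an arm code, or be collected by arm through the separate rooms, and arm-level counts are enough for a blinding index. The trigger itself presupposes such a link, and a condensed article may leave form coding to the full protocol. Even uncoded forms bound the number correct, as the G = 66 and G = 106 cases show, and the reasons for guesses are also collected. So it is too strong to say that neither check can work. What stands is that the text states a rule that depends on the arm and names no route to it.

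A reader might also infer that acting mid-study on correct guesses contradicts the blinding of statisticians. The text does not say that trial statisticians make that comparison, and it refers elsewhere to independent researchers, so no contradiction is shown. It simply names nobody for the task.

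On the assessor half, one can say that decision processes are recorded as well, and that the word judgments may not mean allocation guesses alone. Recorded reasoning is useful, but it does not change the comparison on which the conclusion is to rest. If the judgments were repeat severity ratings, the comparison would be test-retest reliability, which does not show unblinding either.

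Finally, no primary or secondary estimate depends on these checks, and the 0.97-point difference is a planning assumption, not a result. Both are true. They limit the consequence to interpretation of the findings.

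**Conclusion.** The concern holds in two parts of unequal strength.

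The assessor check is wrong as written. Its stated comparison gives 100% agreement under full unblinding and under a repeated chance guess, so it cannot detect what it is meant to detect. This needs no assumption beyond the plain reading of the sentence.

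The participant check is underspecified on a point its own trigger requires. If forms truly lack an arm link, an even split of 53 in 106 leaves the number correct anywhere from 0 to 106. That range assumes complete response and 53 per arm. Because 106 is not a multiple of the block size of 4, the split could be 54 to 52, which changes the range only trivially. If an arm code exists in the full protocol, the remedy here is to state it.

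The change is worth making. It does not affect the validity of the efficacy estimates, but it decides whether the trial can report anything useful on blinding.

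**What to change.** **Assessors.** Replace the comparison of first and repeated judgments. Have each assessor record an allocation guess for the participant after the Week 8 HAMD-17 rating is complete, and compare it with true allocation by arm, with 95% CI, after database lock. Asking only then also avoids prompting assessors to think about allocation at weeks 4 and 6, before the primary rating.

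**Participants.** Keep the mid-study and end-study questionnaires, but put a concealed study or arm code on each form. The key is held by someone independent of assessors, data collectors and analysts. Report correct guesses or a blinding index per arm with 95% CI. Any mid-study comparison is made by that independent person alone.

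**Cost.** One revised form, a named key holder and a few lines of text; treatment, endpoints and sample size do not change. Participants may answer slightly less freely than on an uncoded form. Recruitment began on 1 January 2025, so any forms already collected without a code cannot be recovered, and the report should say how many there were.

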### Outcomes

#### Primary outcome.

The primary outcome is the change in the 17-item Hamilton Depression Rating Scale (HAMD-17) score from baseline to the end of the 8-week treatment period (Week 8). The HAMD-17 is the most employed classical clinical depression symptom rating scale, which measures five domains related to depression, including anxiety/somatization, weight, cognitive disturbance, psychomotor retardation and sleep disturbance [27]. HAMD-17 consists of 17 items that include 3 (scored from 0 to 2) and 5 (scored from 0 to 4) response variants, which reflect ascending symptom severity levels. Total scores are categorized as follows: 0–7 (normal), 8–24 (mild to moderate depressive disorder), and ≥25 (major depressive disorder).

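### Blinded assessors are asked to guess allocation after each assessment, so some guesses can be on record before the primary week-8 HAMD-17 rating (minor)

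*Protocol article*

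**What the plan says.** The Blinding section contains two checks.

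- **Assessors.** It states that "The outcome assessors, data collectors, and statisticians will be blinded to group allocations". It then has the outcome assessors judge the arm of a random selection of cases: "After each assessment, assessors will reassess the group allocations of randomly selected cases without access to their prior assessment results". Their decision process is recorded, and the purpose is given as "The comparison between initial and repeated judgments will be used to assess whether assessors will be influenced".
- **Participants.** "At mid-study and end-study, participants will be asked via anonymous questionnaires to guess their assigned group and provide reasons". The consequence is "If a significant number guess correctly, potential causes will be analyzed and measures will be adjusted". The measures are not named.

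On timing, the abstract says "Evaluations will be performed at baseline and at weeks 4, 6, and 8 after treatment initiation". The Primary outcome section fixes the endpoint as the change in HAMD-17 from baseline to week 8. Under Randomization and allocation concealment, baseline assessments come before the envelope is handed over. A judgement of allocation therefore has meaning only from week 4 onward.

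**The concern.** A blinded rater who has been asked to name a participant's arm and give reasons has formed an expectation. If that rater scores the same participant again, the later score may drift toward the guess. HAMD-17 is a rated symptom scale, and the Discussion itself lists subjective assessment as a possible source of measurement bias. If guesses are right more often than chance, drift toward the guess adds a spurious difference in favour of JTN at the primary visit. The planned difference is less than one point, so even a modest drift is worth avoiding when it costs little to do so.

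The secondary matter is the open wording of the participant clause. The randomised comparison is JTN against one sham procedure. If a mid-study adjustment reached the needling in either arm, early and late participants would be compared on different contrasts. The clause does not say that this is excluded.

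**Working it through.** **The plan's target.** The Sample size calculation section gives mean changes of 10.79 (SD 1.40) and 9.82 (SD 1.80).

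- Difference: 10.79 − 9.82 = 0.97 points.
- Pooled SD: √((1.40² + 1.80²)/2) = √2.60 = 1.612.
- Two-sided 0.05, noncentral t: power is 0.797 with 44 per arm and 0.806 with 45, which reproduces the stated 45.
- Dropout: 45/0.85 = 52.9, so 53 per arm and 106 in total, as stated.
- Standard error of the difference at 45 per arm: 1.612 × √(2/45) = 0.34 points.

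**Order of events.** Allocation judgements follow each assessment, so they can occur after weeks 4, 6 and 8. Those after weeks 4 and 6 come before the primary rating; those after week 8 do not. Nothing in the article delays the judgement until the last rating is done.

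**Size of a possible bias.** The documents give none of the next three quantities, so all are assumptions.

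- s = 0.5: points by which rated improvement is raised for a participant guessed as JTN, or lowered for one guessed as sham.
- p = 0.6 to 0.8: proportion of correct guesses in each arm.
- f: fraction of participants judged before week 8 by a rater who also gives the week-8 score.

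Mean shift among affected JTN participants: p(0.5) − (1 − p)(0.5) = 0.5(2p − 1). Among affected sham participants it is −0.5(2p − 1). The bias in the arm difference is therefore f × (2p − 1) points.

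| p | f = 10% | f = 20% | f = 100% |
|---|---|---|---|
| 0.6 | 0.02 (2%) | 0.04 (4%) | 0.20 (21%) |
| 0.7 | 0.04 (4%) | 0.08 (8%) | 0.40 (41%) |
| 0.8 | 0.06 (6%) | 0.12 (12%) | 0.60 (62%) |

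Percentages are of 0.97. At 10–20% sampled, the largest value, 0.12, is 0.12/0.34 = 0.35 of a standard error. The last column requires every participant to be judged early by a returning rater.

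**The case against.** Several arguments limit the point, and most of them stand.

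- **Only a random selection is judged.** A reader might infer that every selected case is judged at both week 4 and week 6. The text does not say so. Cases may be drawn afresh each time, and some only after week 8, when no harm can follow. The comparison of initial and repeated judgements implies more than one judgement per case, but not at which visits. A bias of 41% of the target would need all participants to be sampled early, which contradicts random selection of cases.
- **Raters are not unblinded.** They are never said to learn the true arm, and the article does not say that one rater sees a participant throughout. Raters may also form impressions unprompted, so only the increment from having to record a guess counts.
- **Improvement alone is a weak clue.** With the planned effect, the best guess from improvement is right with probability Φ(0.97/(2 × 1.612)) = Φ(0.30) = 62%. That gives 2(0.62) − 1 = 0.24 points if everyone is sampled, and about 0.05 at 20%. With no true effect it gives 50% and no bias. Higher accuracy needs another source, such as participants' remarks about needle sensation.
- **The participant clause is conditional.** A reader might infer that the plan alters the sham or JTN procedure part-way. The clause stands beside separate rooms and supervised conversation, and tightening those is its natural meaning. The Intervention section provides for no change to the needling. Repairing a failing safeguard during the trial is defensible, and a threshold or decision-maker may well be in the full protocol.

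What remains is the timing: as written, some assessor judgements precede the primary rating, and nothing shown prevents the same rater from returning.

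**Conclusion.** The point holds as a minor one. Following the Blinding section as written lets some blinded assessors record an arm guess before the week-8 HAMD-17. On the assumed half-point shift and 60–80% accuracy, the bias is about 0.02–0.12 points (2–12% of the target) at 10–20% sampled. It reaches 21–62% only if everyone is sampled early. The shift, the accuracy, the sampled fraction and the returning rater are all assumptions, so these figures illustrate scale and do not estimate what will happen.

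The documents do not support a claim that the randomised contrast will change during the trial. They leave the word for the measures undefined, and a sentence of clarification is enough.

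**What to change.** 1. Collect the assessor's allocation judgement once per selected participant, only after that participant's week-8 HAMD-17 has been recorded and locked. If the comparison of initial with repeated judgements is to be kept, take both after the lock.
2. State that any adjustment prompted by the mid-study participant guesses is limited to blinding safeguards, such as room separation and supervision of conversation, and does not alter the JTN or sham procedures.

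The cost is a wording amendment and fewer assessor forms. The downside is that assessor unblinding is learned later. The Trial design section gives recruitment as already under way, so the change can protect only participants who have not yet reached week 8. The date it takes effect should be recorded.
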